#### Analyses

First, general descriptive statistics will be used to describe personal characteristics of the participants, as well as findings concerning current health behaviour status, adherence to the public health guidelines and socio-cognitive characteristics. Second, logistic regression analyses will be conducted with re-visits to the program and level of behaviour change as dependent variables. Furthermore, linear regression analyses will be conducted with number of re-visits, duration of re-visits and number of behaviours selected as dependent variables. Demographics, such as gender, height, weight, marital status, religious background, ethnicity, educational level, current work status, and income, health behaviour status and cognitions (measured at baseline) will be included in the model as predictors of the dependent variables.

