### Design

The second study consists of a randomized control trial (RCT) including one experimental group. A design with a baseline measurement and three follow-up measurements (6, 12 and 18 months) measuring health behaviour status, intention to change, cognitive variables and planning abilities, will be used to compare the experimental condition (use of a proactive technique) to a control condition (use of a reactive approach).

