### Outcome measures

The primary outcome measures are re-visits to the program and level of behaviour change. Program revisits are objectively monitored for a total period of eighteen months. Recordings will be done anonymously and will yield information about the number of times the program is visited, the duration of each visit (in minutes) and which specific behaviours are most frequently selected. Level of behavioural change is assessed by studying participants' adherence to public health guidelines set for these behaviours (0 = not complying with recommendations/1 = complying with recommendations).

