### Statistical analysis

#### Sample size and power

With regard to re-visits to the program (first primary outcome measure), it is estimated that approximately 50% of the respondents of the no-prompting condition will visit the site more often than four times (after the baseline, and the first three post tests after six, twelve and eighteen months). It is estimated that in the prompting condition 70% of the respondents will visit the site more than four times. Power calculations reveal that in order to be able to detect this difference with a power of 80% (p = .05) at least 186 persons per condition are needed. Taking into account potential attrition, it is proposed to collect the data of 250 persons per cell.

The second primary outcome measure is the level of health behaviour change. The current program entails a total of five health behaviours. Therefore, with regard to the assessment of behaviour change (second outcome measure), estimations for finding effects will be based on smoking, since this behaviour results in the most conservative power calculations. Approximately 25% to 30% of the population smoke [51]. Power estimations are based on the ability to detect a difference in quit rates of 10% with a power of .80 and a *p*-value of .05. It is estimated that, in order to detect this significant difference in quit rates, 219 smoking persons per cell are needed, resulting in a total of 438 smokers [52]. To be able to have 438 smokers in the sample (under the condition that 30% of the Dutch population smokes), 1575 participants need to be recruited. Accounting for 35% attrition during the trial period, the total sample size for this study will be approximately 4500 persons.

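### The only model named for guideline compliance, a primary outcome measured at 6, 12 and 18 months with 35% attrition stated, is logistic regression on baseline predictors, with nothing that links the waves or uses interim answers

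*Protocol article*

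**What the plan says.** All references are to the protocol article, Study 2.

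- **Design** and **Recruitment and procedure**: health behaviour is measured at baseline and at 6, 12 and 18 months. Both arms are invited to these measurements by e-mail. Only the experimental arm is also prompted every three months, for 18 months, to return to the program.
- **Outcome measures**: behaviour change is one of two primary outcomes, coded "0 = not complying with recommendations/1 = complying with recommendations". Program re-visits, the other, are monitored objectively.
- **Sample size and power**: the behaviour-change calculation rests on "the ability to detect a difference in quit rates of 10% with a power of .80" among smokers. It continues: "Accounting for 35% attrition during the trial period, the total sample size for this study will be approximately 4500 persons".
- **Analyses**: "logistic regression analyses will be conducted with re-visits to the program and level of behaviour change as dependent variables". Demographics are predictors, and "health behaviour status and cognitions (measured at baseline) will be included in the model as predictors of the dependent variables". The other model named is linear regression, for number and duration of re-visits and number of behaviours selected.

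The Analyses section names no follow-up time for compliance, no model that joins the three measurements, and no use of interim answers.

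**The concern.** A logistic regression takes one binary outcome per person. Compliance yields up to three, and over a third of participants are expected to be lost. If the model is fitted to those who answer at 18 months, a participant who answered at 6 and 12 months and then left contributes nothing to the 18-month comparison. That loses precision.

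The more serious risk is bias. The intervention is itself a form of repeated contact, so prompting may change who keeps answering questionnaires. If those who have not changed their behaviour are also more likely to leave, the 18-month responders in the two arms are selected to different degrees, and an arm difference can appear where none exists. Interim behaviour is the information that could correct this, and a responders-only model does not use it.

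**Working it through.** **1. Inputs from the article.** Three follow-ups; 35% attrition; total about 4500; 30% smokers; planned difference 10 points in quit rate; 219 smokers per cell.

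**2. The article's own figures.**
- 219 per cell reproduces for 10% versus 20%, two-sided 0.05, power 0.80, with continuity correction (199 without). The 10% base rate is inferred, since only the difference is given.
- 1575/(1 − 0.35) = 2424 (rounded up), not 4500, whereas 1575/0.35 = 4500. The total therefore matches 65% attrition rather than the stated 35%, and the level of attrition is itself uncertain.
- Smokers per arm at the stated total: 4500 × 0.30 / 2 = 675.

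**3. Illustrative model with no true arm effect.** None of these inputs is in the article. Quit rate at 6 months 15%; over each later six-month interval a quitter stays quit with probability 0.75 and a smoker quits with probability 0.05; 88% answer at 6 months; per interval, quitters are retained with probability 0.95 and smokers with probability r, which differs by arm.

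True quit rate in both arms:
- 12 months: 0.15 × 0.75 + 0.85 × 0.05 = 0.155
- 18 months: 0.155 × 0.75 + 0.845 × 0.05 = 0.1585

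Prompted arm, r = 0.88, as a fraction of 6-month responders:
- Retained to 12 months: quitters 0.15 × 0.95 = 0.1425; smokers 0.85 × 0.88 = 0.748
- Status at 12 months: quit 0.1425 × 0.75 + 0.748 × 0.05 = 0.1443; smoking 0.8905 − 0.1443 = 0.7462
- Retained to 18 months: 0.1443 × 0.95 + 0.7462 × 0.88 = 0.1371 + 0.6567 = 0.7937
- Overall retention: 0.88 × 0.7937 = 70%
- Responder quit rate: (0.1371 × 0.75 + 0.6567 × 0.05)/0.7937 = 17.1%

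The same steps for the control arm:

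| Control r | Retention, control vs prompted | Responder quit rate, control vs prompted | False difference |
|---|---|---|---|
| 0.81 | 61% vs 70% | 18.6% vs 17.1% | −1.5 points |
| 0.80 | 60% vs 70% | 18.8% vs 17.1% | −1.7 points |
| 0.75 | 54% vs 70% | 20.1% vs 17.1% | −3.0 points |

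Type I error of a nominal 5% test with 675 smokers per arm:
- 61% vs 70%: standard error √(0.186 × 0.814/412 + 0.171 × 0.829/471) = 0.0258; 0.0147/0.0258 = 0.57; rejection about 9%.
- 54% vs 70%: standard error √(0.201 × 0.799/364 + 0.171 × 0.829/471) = 0.0272; 0.0297/0.0272 = 1.09; rejection about 19%.

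In simulations of this model, a likelihood analysis of all waves had bias below 0.1 point. The responders-only estimate had 1.24 to 1.34 times its variance.

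**4. Which conditions are needed.** A second simulation, again with no true effect, took the whole sample at about 50% compliance (assumed) with average attrition about 35%. Odds ratios (OR) are for 18-month responders.

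| Drop-out mechanism | OR, unadjusted | OR, adjusted for baseline compliance | Adjusted type I error, N = 1574 / 4500 |
|---|---|---|---|
| Same in both arms | 1.00 | 1.00 | 6% / 5% |
| Unequal (44% vs 26%), unrelated to compliance | 1.01 | 1.01 | 4% / 5% |
| Unequal (44% vs 25%), related to compliance | 0.90 | 0.95 | 6% / 10% |
| Related to compliance in one arm only | 0.86 to 0.80 | 0.93 to 0.90 | 7–13% / 15–26% |

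Weighting by the earlier answers gave 0.995 to 1.005 throughout. So bias needs drop-out tied to both interim behaviour and arm, and baseline adjustment roughly halves it.

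**5. Smokers.** Everyone in the quit-rate comparison is non-compliant on smoking at baseline. That covariate is constant there, so adjusting for it removes nothing. Baseline cognitions and demographics might remove a little.

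**The case against.** The strongest reply is that the article does not state the analysis being criticised. A reader might infer from the Analyses section that the model is ordinary logistic regression on completers and that earlier answers are discarded, or that waves are stacked as independent. The text says none of these. It uses the plural and does not exclude one model per visit, a repeated-measures logistic model or imputation. Missing-data handling is commonly left to a fuller document. This stands: silence on missing data is not the point here. What remains is that a method is named for a primary outcome measured three times and, as named, it does not join the waves. Separate models per visit would use earlier answers only at those visits; the 18-month contrast would still rest on responders.

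A reader might also infer that 35% attrition produces a false difference by itself. It does not; unequal attrition unrelated to behaviour is also harmless. Both required links are assumptions. Both arms receive the same follow-up invitations, and the extra prompts invite a program visit rather than a questionnaire.

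The planned baseline predictors do reduce the bias in the whole sample, and that must be credited. The loss of precision matters less if 4500 are recruited and attrition is 35%: 675 × 0.65 is about 439 smokers per arm, twice the 219 required. The direction of the illustrated bias, against prompting, follows from assuming that prompts mainly retain continuing smokers.

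**Conclusion.** The point holds in a limited form. The article names a model family that, as named, neither connects the three compliance measurements nor uses drop-outs' interim answers for the 18-month comparison. If fitted to 18-month responders, it loses precision and is open to a false arm difference of about 1.5 to 3 points in quit rate, against a planned 10, with type I error of about 9% to 19% at 675 smokers per arm.

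Those sizes rest on assumed quit transitions and on assumed retention that differs by arm and by interim status. They are illustrations, not predictions. The 675 comes from a total that does not follow from 35% attrition; the false difference does not depend on it, but the type I error does.

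The documents do not support saying that the planned analysis discards data or is biased as planned. They support saying that the named method should be replaced by one that uses all waves. The point does not extend to re-visits, which are logged objectively and are not exposed to questionnaire drop-out.

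**What to change.** For the compliance outcome only:

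- Name one repeated-measures (mixed-effects) logistic model per behaviour, using all available 6-, 12- and 18-month answers, with condition, time, condition × time and the planned baseline predictors. Multiple imputation from earlier waves followed by logistic regression is an acceptable alternative.
- State in advance which follow-up contrast is primary. Eighteen months, the end of the prompting period, is a natural choice, but the article does not require it.

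**Cost.** A change of analysis wording and a somewhat more complex model, with no new data or participants. The analysis relies on missing-at-random, a weaker assumption than a responders-only analysis needs. The correction may not be perfect: a check with a random-intercept logistic model left residual bias of 0.1 to 0.3 points in the illustrative setting.

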### Measures

#### User characteristics

User characteristics are collected to produce a detailed user profile entailing information on personal characteristics, health behaviour status as well as socio-cognitive characteristics. Questions used in the Health Monitor pertaining to personal characteristics, included questions on gender, height, weight, marital status, religious background, ethnicity, educational level, current work status, and income. Furthermore, questions used in the Health Monitor pertaining to physical activity [40], fruit and vegetable intake [41], alcohol intake [43] and smoking behaviour [44] were used to assess health behaviour status. Finally, several determinants of health behaviour as mentioned in the I-Change model were used as socio-cognitive characteristics; intention, attitude, social influence, self-efficacy, action and coping planning.

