### Recruitment and procedure

The research sample consists of individuals that participate in the Dutch Adult Health Monitor and that decide to pay a first visit to the new CT program. After logging in to the program at baseline and consenting to participation by filling out an online informed consent form, participants are randomly assigned to one of the two conditions. People in the experimental condition are reminded proactively via e-mail every three months for a period of 18 months to visit the CT program in order to obtain iterative feedback concerning their health behaviour status and additional CT advice, whereas people in the control condition do not receive any additional prompts and are only encouraged to re-visit the program in the future at baseline. All participants will be invited by e-mail for the follow-up measurements at 6, 12 and 18 months (Figure 2.).

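### The single long covariate list in Study 2 leaves few quits per parameter in the smoking comparison and modestly inflates a non-null odds ratio for condition

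*Protocol article*

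**What the plan says.** Study 2, Analyses, plans logistic regressions for re-visits and for level of behaviour change, and linear regressions for number of re-visits, duration of re-visits and number of behaviours selected. One predictor list serves them all. It gives nine demographics as examples (gender, height, weight, marital status, religion, ethnicity, education, work status, income) and adds that "health behaviour status and cognitions (measured at baseline) will be included in the model as predictors of the dependent variables". No shorter model is given for comparing the two conditions.

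Study 1, User characteristics, names the cognitions as "socio-cognitive characteristics; intention, attitude, social influence, self-efficacy, action and coping planning". Intervention materials divides several of these further: attitude into pros and cons, social influence into norm, modelling and support, and intention into two items.

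Study 2, Sample size and power, bases the behaviour outcome on smoking: "219 smoking persons per cell are needed, resulting in a total of 438 smokers". It then states: "Accounting for 35% attrition during the trial period, the total sample size for this study will be approximately 4500 persons".

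**The concern.** Smoking cessation is the behaviour on which the second primary outcome was powered, and it is a binary outcome with few events. Maximum-likelihood logistic regression with few events per parameter pushes non-null odds ratios away from 1 and can fail to converge. A randomised comparison does not need a long covariate list to be valid, so the model accepts this bias without needing to.

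The list may also limit who can be analysed. Content of the CT program says that the cognitions come from an additional tailoring questionnaire, with one module per behaviour. Study 1, Outcome measures, treats the intention question as the first question of a module. If smoking cognitions are collected only in the smoking module, a model that requires them could exclude randomised smokers who never open it. Study 2, Design, lists cognitive variables at the baseline measurement, so the article leaves this unclear.

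**Working it through.** **1. Reproduce the plan's figure.** Sample size and power gives a 10-point difference in quit rates, power .80 and p = .05, but no base rates. Take 10% v 20%, two-sided:

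n = [1.96·√(2·0.15·0.85) + 0.8416·√(0.10·0.90 + 0.20·0.80)]² / 0.10² = (0.990 + 0.421)² / 0.01 ≈ 199.

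With continuity correction: (199/4)·[1 + √(1 + 4/(199·0.10))]² ≈ 219, an exact match. Other 10-point pairs, two-sided with correction, give 160 (5/15), 270 (15/25) and 313 (20/30). The rates 10% v 20% are therefore inferred.

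**2. Expected quits.**
- Powered minimum: 219·0.10 + 219·0.20 = 65.7.
- Stated size, with the plan's 35% attrition and 30% smoking: 4500·0.65·0.30 = 877.5 smokers; ·0.15 = 131.6 quits.
- Stated size at 25% smoking, the lower figure given: 4500·0.65·0.25 = 731 smokers; 109.7 quits.

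**3. Parameters.** The article gives no coding. With one parameter each: condition 1 (not in the list, but needed for a comparison) + demographics 9 + behaviours 5 + constructs 6 = 21, or 20 if baseline smoking status is constant among smokers. With ten cognition scores and four other behaviours: 1 + 9 + 4 + 10 = 24. If the six categorical demographics have 3 to 5 categories each (assumed), about 37.

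**4. Quits per parameter.**

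| Smokers analysed | Quits | 21 terms | 24 terms | 37 terms |
|---|---|---|---|---|
| 438 | 65.7 | 3.1 | 2.7 | 1.8 |
| 731 | 109.7 | 5.2 | 4.6 | 3.0 |
| 877.5 | 131.6 | 6.3 | 5.5 | 3.6 |

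**5. Simulated effect.** Each setting had 2000 trials. Covariates were half binary and half normal, with no or moderate prognostic effect.

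- *438 smokers:* the log odds ratio was inflated by 7–10% with 24 parameters and 13–16% with 37 (for 37: true 2.25 estimated as 2.50; true 2.38 as 2.74). Coverage of the 95% interval was 92–94.5%, type I error 4.9–6.2%, and 3–5% of fits failed to converge.
- *876 smokers:* inflation 3–6% (true 2.38 estimated as 2.51 with 37), coverage 94–95%, type I error 4.5–5.8%.
- *True effect nil:* no bias at either size.

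The difference between the true values 2.25 and 2.38 is non-collapsibility, not bias.

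A second set, with three prognostic covariates and 219 per arm, gave a median odds ratio of 2.54 (37 parameters) and 2.47 (24) against a true 2.31. Type I error was 7.1% (Wald) and about 5.4% respectively. A four-parameter model gave 2.30–2.32, about 5% error and the same power, 84%. A further run gave inflation of 7–15% at 438 smokers and 3–7% at 878.

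**6. Loss of smokers.** From 438, losing 10% gives power .796 without continuity correction and .754 with it. From 878, power is still .837 or .801 after losing 50%. From 731, it is .837 or .802 after losing 40%.

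**The case against.** The strongest reply is that 438 is a minimum and 4500 is the stated target. About 878 smokers and 132 quits would then be analysed, and the inflation is only 3–7%. This stands, so both sizes are shown. It is not a complete answer, because the route to 4500 does not follow from the plan's own steps: 1575/0.65 ≈ 2423, which would leave 1575·0.30 ≈ 472 smokers and about 71 quits, close to the minimum.

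The parameter count above 21 is also an assumption, and the largest distortions combine the longest coding with the smallest sample. That stands too.

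A reader might infer that confidence intervals would be seriously too narrow. The simulations do not show this: coverage falls short by 0 to 3 points at 438 smokers and about 0 to 1 point at the planned size.

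A reader might also infer that complete-case analysis would take power below .80. The article states no missing-data rule, and such a rule is commonly left to the full protocol or analysis plan. At the planned size about 40–55% of retained smokers would have to be lost first.

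Finally, if many of the cognitions predict quitting strongly, adjusting for them could add power. Simulations with few or moderate prognostic effects cannot rule that out.

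The covariate list itself is not a detail left open: the article says that these variables will be in the model.

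**Conclusion.** The point holds as a modest, avoidable bias in one part of a primary outcome. Followed as written, the list gives about 2–3 quits per parameter at the powered minimum and about 3–6 at the stated size. A real effect on smoking cessation would be overstated by about 7–16% on the log odds scale in the first case and 3–7% in the second. At the smaller size there is also slight under-coverage, type I error of about 5–7% and occasional non-convergence. An effect would not be created where none exists.

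This rests on the inferred 10% v 20% rates, the assumed coding and the assumed covariate distributions. It concerns smoking: the bias does not arise in the linear regressions, and the re-visit outcome and the other behaviours are not restricted to the smokers. Exclusion of smokers through missing cognitions is a conditional risk, and no loss of power below .80 is shown at the planned size.

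**What to change.** In Study 2, Analyses, separate two models.

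1. **Trial comparison.** Randomised condition plus a short, named set of baseline covariates available for all randomised participants, for example the baseline level of the same behaviour (cigarettes per day for smoking). Handle baseline gaps by simple imputation or a missing indicator, so that no randomised person is dropped for a missing covariate.
2. **Exploratory predictor model.** The full list of demographics, behaviour status and cognitions, labelled exploratory, with Firth or other penalised estimation for smoking.

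Also state whether baseline cognitions are collected from everyone or only from those who open a module.

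The cost is wording only, with no new data. The downside is that the trial estimate is adjusted for fewer covariates.

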#### Content of the CT program

The CT program uses a step-by-step approach to guide people towards behaviour change. After online completion of the Adult Health Monitor people are informed in detail on the embedded program and the accompanied studies. People that indicate to be interested in the program are subsequently linked to the program. During their first visit demographic data (age, gender, height, weight, religious background, ethnicity, educational level and income) and personal data concerning the target health behaviours, acquired through the Adult Health Monitor questionnaire, are transferred to the CT program and used to inform people on the current status of their health behaviours by comparing these to Dutch public health guidelines (i.e. being moderately physically active for 30 minutes at least 5 days a week, eating 2 pieces of fruit per day, eating 200 grams of vegetables per day, not drinking more than one (women) or two (men) glasses of alcohol a day and non-smoking). In case of discrepancies, people are alerted and provided assistance in changing their health behaviour(s) with help of CT advices available per behaviour.

Changing health behaviours with help of computer tailoring is the main component of the program. A CT module is available per health behaviour and within each module people have the opportunity to obtain personalized advices regarding the opted health behaviour. All health behavioural advices are adapted to individuals' characteristics by considering demographic, behavioural and social-cognitive variables [24,45,46]. Some variables, such as individuals' current health behaviours and characteristics of the respondent (gender), are directly obtained through the Adult Health Monitor. Other variables, such as cognitive variables with regard to the health behaviour (attitude, perceived social influence and self-efficacy), intention to change the health behaviour and planning strategies (action plans and coping plans) are assessed by using an additional tailoring questionnaire. All tailoring components are based on the Integrated Model for exploring motivational and behavioural Change (I-Change Model) [47].

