### Outcome measures

To measure the adoption level of the new CT program focus will be on level of first use, demographic and behavioural characteristics of users and non-users, satisfaction with the program, characteristics of satisfied and unsatisfied users, intention to re-visit the program and frequency of re-visits. In order to measure level of first use of the program, two dichotomous variables will be created; one indicating whether participants initiate a behaviour change module and one indicating whether participants finish the module. Initiating a module is labelled as "yes" when people fill out the first question of this module, which is the question concerning intention to change the specific health behaviour. Completion of a module is labelled as "yes" when people also fill out the final question of the module. Re-visiting of the program will be assessed monitoring whether participants log in to the program within a three month period after baseline (0 = yes/1 = no). Re-visits to the program will be measured by comparing the dates of log-in to the baseline date.

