### Statistical analysis

First, general descriptive statistics will be used to describe personal characteristics of the participants, as well as main findings concerning current health behaviour status, adherence to the public health guidelines and socio-cognitive characteristics. Second, logistic regression analyses will be conducted with initiation of a module, completion of a module and revisiting of the program as dependent variables. Demographics, such as gender, height, weight, marital status, religious background, ethnicity, educational level, current work status, income, health behaviour status and cognitions (measured at baseline) are included in the model as predictors.

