### Study 2. Increasing sustained use of the CT program

The aim of this study is to test the effect of using a proactive approach (i.e. periodic e-mail prompting) on revisiting of the program compared to a reactive approach. Furthermore, the efficacy of these approaches with regard to behaviour change will be studied.

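### The Study 2 models for both primary outcomes name no term for the randomised condition, and the cognitions they list may exist only for participants who opened a module

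*Protocol article*

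**What the plan says.** The opening of Study 2 sets the aim to "test the effect of using a proactive approach (i.e. periodic e-mail prompting) on revisiting of the program compared to a reactive approach", and adds that effects on behaviour change will be studied too. The Design section says that the measurements at baseline, 6, 12 and 18 months "will be used to compare the experimental condition (use of a proactive technique) to a control condition (use of a reactive approach").

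The Study 2 Analyses section then gives the models: "logistic regression analyses will be conducted with re-visits to the program and level of behaviour change as dependent variables". Linear regressions follow for the number and duration of re-visits and the number of behaviours selected. On the terms in these models it lists demographics one by one, adds behaviour status and baseline cognitions, and says that these "will be included in the model as predictors of the dependent variables". No other term is named.

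On where the covariates come from, Content of the CT program says that demographics and behaviour data are transferred from the Adult Health Monitor. Attitude, social influence, self-efficacy, intention and planning, by contrast, "are assessed by using an additional tailoring questionnaire". The Study 1 Outcome measures section defines starting a module as answering its first question, "which is the question concerning intention to change the specific health behaviour".

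**The concern.** In a two-arm trial the primary model has one essential term, the randomised condition. Here the model's terms are listed down to height and religious background, and that term is absent. A model fitted to the list would show which kinds of people re-visit or change behaviour, pooled over arms. It would not answer the trial's question for either primary outcome.

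Adding the condition to the list may not be enough. If cognitions are recorded only inside a module, they are missing for each behaviour whose module a participant never opened. Software that drops incomplete records would then restrict the randomised comparison to module openers, a smaller and self-selected group, unless the handling of these values is specified.

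**Working it through.** **1. The two predictor lists side by side.**
- Study 1, Statistical analysis: gender, height, weight, marital status, religious background, ethnicity, education, work status and income, and "health behaviour status and cognitions (measured at baseline) are included in the model as predictors". Study 1 has no arms, so no condition term is expected.
- Study 2, Analyses: the same demographics in the same order, then behaviour status and cognitions. Study 2 has two arms, and condition, group or prompting is not mentioned in the paragraph.

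The near-identity suggests that the list was carried over from Study 1. With only these terms in the model, no coefficient corresponds to prompting.

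**2. Who has each covariate.**
- Demographics and behaviour status come from the Monitor, so they are held for every consenting participant.
- Cognitions: Content of the CT program and Intervention materials place them in the online questionnaires that feed the tailored advice for each behaviour. Study 1 Outcome measures places the intention item at the start of a module. Against this, Study 2 Design lists intention, cognitive variables and planning in the baseline measurement, with no limit to module openers. The sections do not settle the matter.

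**3. Would restriction to openers bias the contrast?** Cognitions are taken at baseline, and by the Materials section the first prompt is sent three months after the first visit. Opening a module at baseline therefore cannot depend on prompting. A simulation checked this: 1000 runs, 186 per arm, re-visit rates 50% and 70%, condition in the model, opening independent of arm, same effect in openers and non-openers. The true odds ratio is (0.7/0.3)/(0.5/0.5) = 2.33. The estimates were 2.35 in everyone, 2.35 with 60% openers and 2.37 with 40% openers. At that sample size power fell from 97% to 86% and 70%.

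**4. Possible loss for quitting.** The plan's own figure comes first. The article gives a 10-point difference but no base rate, so 10% v 20% is assumed. Two-sided 0.05, 80% power:

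n = (1.96 × √(2 × 0.15 × 0.85) + 0.842 × √(0.09 + 0.16))² / 0.10² = 199 per arm, or 219 with continuity correction. This matches the stated 219 per cell.

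Smokers retained, using the plan's 4500 participants, 35% attrition and 30% smokers: 4500 × 0.65 × 0.30 = 877.5, or about 439 per arm.

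Power = Φ[(0.10 × √n − 1.96 × √0.255) / 0.5], without continuity correction:

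| Share of smokers opening the smoking module (assumed) | n per arm | Power |
|---|---|---|
| 100% | 438.75 | 98.6% |
| 50% | 219.4 | 83.7% |
| 40% | 175.5 | 74.9% |
| 30% | 131.6 | 62.4% |

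**5. Possible loss for re-visits.** If 30% of the 4500 × 0.65 = 2925 retained participants had complete cognitions, about 439 per arm would remain. Power for 50% v 70% would still exceed 99.9%.

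**The case against.** The strongest reply is that silence is not exclusion. The Analyses section says that the listed covariates go into the model; it does not say that nothing else does. The aim, the Design section, the Discussion and a sample-size calculation based on 50% v 70% between conditions all show that the arms will be compared. The article is condensed, and a fuller specification may exist. This stands as far as intent goes: a reader might infer that no between-arm comparison is planned, and the document does not support that. It does not rescue the stated model. The article chose to list the terms in detail and left out the one that carries the trial's question.

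The objections on the cognitions have more force. A reader might infer that all the covariates are limited to module openers; demographics and behaviour status are not. Study 2 Design lists the cognitions at baseline without restriction, so their absence in non-openers is an inference. The article does not prescribe complete-case deletion. A reader might also infer that restriction to openers would bias the comparison; because the cognitions precede the first prompt, it would not do so by itself. Finally, adjusting a randomised comparison for prognostic baseline cognitions is legitimate where they are held for everyone.

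**Conclusion.** The point holds as a badly specified primary model. As written, neither primary outcome has a coefficient for prompting, and this conclusion needs no assumption beyond the text.

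The second part is conditional. If cognitions exist only for module openers, and incomplete records are dropped, the comparison shrinks to openers. The cost is sample size and generalisability, and an effect that differs between openers and non-openers would be estimated for openers only. The size is uncertain, because both the opening shares and the 10% base quit rate are assumed. At 50% opening, power for quitting stays above the planned 80%; at 40% or 30% it falls below. The re-visit outcome is not threatened at the planned sample size.

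**What to change.** In the Study 2 Analyses section, state for each primary outcome a logistic regression with randomised condition (prompting v no prompting) as the tested term, and report its estimate with a confidence interval. Fit it in all randomised participants, and for quitting in all baseline smokers.

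Adjust the primary model only for baseline covariates held for everyone from the Monitor. Move the cognitions to a secondary predictor analysis, or keep them and state how missing values are handled. Reconcile the Study 2 Design section with Content of the CT program and the Study 1 Outcome measures section, so that it is clear who provides cognitions at baseline.

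The cost is wording only, with no new data. The small downside is that, if the cognitions are moved, the primary estimate is no longer adjusted for them.
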